### Statistical methods

The EpiData [46] and Statistical Package for the Social Sciences [47] applications will be used for data entry and analysis, respectively. The statistical calculations will be performed on an intention-to-treat basis, where patients will be analyzed as initially randomized. Continuous variables will be expressed as mean ± standard deviation. The Kolmogorov-Smirnov test will be used to test sample distribution. The analysis strategy will be based on differences of MLHFQ and SF-36 scores, DRPs outcome, and six-minute-walk test results between the control and intervention groups. For quality-of-life questionnaires and the six-minute-walk test, the Student’s *t* test will be used if sample distribution proves to be normal. Otherwise, the Wilcoxon rank-sum test will be used. For DRPs and compliance, cumulative incidence and relative risks will be estimated with their respective 95% confidence intervals, and will be used to test differences. The null hypothesis will be rejected at *P <* 0.05.

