### Sample size calculation

Sample size calculation was based on previous work of the literature that evaluated pharmaceutical care and quality of life in patients with HF [21]. We estimated that 40 patients per group would be needed to detect a difference in quality of life on SF-36 of 10.3 points, allowing a standard deviation of up to 10.9 points, one-sided 1% significance, and 95% power. As we expect loss during follow-up of at least 10% of the study participants, 88 participants (44 per group) will be required (Table 1).

**Table 1 T1:** Sample size calculation according to scenarios of benefit in terms of quality of life for patients

**Parameter**	**Groups**		**Sample calculation**
	**Control group**	**Intervention group**	
Quality of life, mean (standard deviation)	52.8 (10.9)	63.1 (10.1)	
Significance level	1.0%	1.0%	
Power of test	95.0%	95.0%	
*N*	40 patients	40 patients	
*N* + 10% (in each group)	44 patients	44 patients	
Ratio	1:1	1:1	
Total	44	44	88

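### A normality test on the trial's own outcome data picks between the t test and the rank-sum test, so the primary comparison need not test the mean difference the trial is sized for

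*Protocol article*

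**What the plan says.** The Statistical methods section of the Protocol article sets a two-stage rule for the quality-of-life questionnaires (the primary endpoint) and the six-minute-walk test (a secondary endpoint). First, "The Kolmogorov-Smirnov test will be used to test sample distribution". Then Student's t "test will be used if sample distribution proves to be normal". "Otherwise, the Wilcoxon rank-sum test will be used". The text does not give the level of the Kolmogorov-Smirnov (KS) test, whether the Lilliefors correction applies, or whether the arms are pooled.

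The same section adds, without condition, "Continuous variables will be expressed as mean ± standard deviation". It plans relative risks with 95% confidence intervals for drug-related problems and compliance, and names no between-group estimate or interval for quality of life. The significance threshold is P < 0.05.

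The Sample size calculation section is built on means: 40 per group are "needed to detect a difference in quality of life on SF-36 of 10.3 points", "allowing a standard deviation of up to 10.9 points", with Table 1 showing means of 52.8 and 63.1. The Discussion expects an improvement of at least ten points on both questionnaires.

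**The concern.** The two tests answer different questions. The t test compares means, which is the quantity used for sizing. The rank-sum test asks whether values in one arm tend to exceed those in the other, and it matches a difference in points only if one distribution is a shifted copy of the other. Under the rule, the outcome data decide which question is answered.

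In the rank-sum branch the report would show means and standard deviations beside a P value that does not, in general, test the difference between them. Read score by score (the natural reading, though not written out), the rule can also send the eight SF-36 subscales, the two summary scores and the Minnesota total to different tests within one primary endpoint. At stake is a fixed hypothesis and effect measure for the primary outcome, not the number of patients.

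**Working it through.** **1. The plan's own figure.** Inputs from Sample size calculation: difference 63.1 − 52.8 = 10.3, SD 10.9, power 95%, significance 1%. The comparison-of-means formula is n = 2·SD²·(z_α + z_β)²/difference².
- Two-sided 1%: 2 × 10.9² × (2.576 + 1.645)² / 10.3² = 39.9, so 40. This reproduces the plan.
- One-sided 1%, as the text labels it: 2 × 10.9² × (2.326 + 1.645)² / 10.3² = 35.3, so 36.

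The label mismatch is a separate matter. What counts here is that 40 comes from a formula for means.

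**2. How often the gate selects the rank-sum test.** Simulation with 40 per arm, no treatment effect, gate at 5%, 5,000 runs. The distributions are assumed, since the protocol gives only means and SDs.

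| Score distribution | Lilliefors, each arm | Lilliefors, pooled | Uncorrected KS, pooled |
|---|---|---|---|
| Normal | 9.5% | 4.8% | about 0% |
| Moderate skew (gamma, shape 4) | 55% | 59% | 5% |
| Strong skew (gamma, shape 1.5) | 92% | 97% | 41% |

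The same data can therefore get different primary tests under different readings of one sentence.

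**3. Chance that the scores split.** There are 8 subscales + 2 summaries + 1 Minnesota total = 11 scores. If all are normal and independent:
- one 5% test per score: 1 − 0.95^11 = 43%;
- one 5% test per arm per score (Lilliefors): 1 − 0.95^22 = 68%;
- uncorrected KS: about 0%, because it almost never rejects normal data once mean and SD are estimated from the sample.

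Independence is not the driver. In small simulations that varied the correlation between scores, Lilliefors in each arm gave 67-70%, Lilliefors pooled 31-35%, and uncorrected KS in each arm under 1%.

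**4. Operating characteristics, same shape in both arms** (normal and the two gammas, two-sided 5%, Lilliefors gate in each arm or pooled). Type I error of the two-stage rule was 4.6-5.7%; the simulation error is √(0.05 × 0.95/5,000) = 0.3 percentage points. Power for a shift of 10.3/10.9 SD was 98-99.7%. If the rank-sum test is used on truly normal data, power at two-sided 1% is 94.0% against 95.1% for a test of means (efficiency 3/π).

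**5. Operating characteristics, different shapes with equal mean and SD** (assumed normal against exponential, 40 per arm, two-sided 5%). With Lilliefors in each arm, the t test rejected in 5.5%, the rank-sum test in 9.3% and the two-stage rule in 9.4%, with the rank-sum test chosen in 90% of runs. A further run of 10,000 gave 5.1% for the t test and 9.3% for the rank-sum test. The two-stage rule gave 9.3% (Lilliefors, each arm), 8.2% (Lilliefors, pooled), 7.0% (uncorrected, each arm) and 5.4% (uncorrected, pooled). So 8-9% belongs to the Lilliefors versions; an uncorrected gate usually stays with the t test.

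**6. What a fixed comparison of means gives up.** For strongly skewed scores (assumed gamma, means 35 and 25, SD about 20, 40 per arm), power was about 62% for the unadjusted t test and 76% for the rank-sum test.

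**The case against.** The best defence is that the rule is written in advance, leaves the analyst no discretion, and does little harm. With same-shape distributions neither error rate moves noticeably. The inflation needs a contrast in shape that nothing in the protocol predicts: the only distributional figures, in Table 1, lie well inside a 0-100 scale. The KS variant and level are details that a fuller document may fix. All of this stands, and it limits the size of the point. It does not reach the core, because the data-driven choice is stated outright, and filling in the variant would leave it in place.

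A reader might also infer more than the text supports:
- **That the sample size or type I error is generally wrong.** Step 4 shows otherwise.
- **That 68% is the chance of a split.** It is the top of a range and needs the Lilliefors version in each arm, which the protocol does not state.
- **That the gate wrongly rejects normal scores at its nominal level.** This is false for the uncorrected test, which almost never rejects them.
- **That no effect in points would be reported.** Means and SDs are shown in either branch, and a rank analysis can carry a shift estimate in points. The mismatch lies between those means and the P value.
- **That neither test can use the baseline value.** Change scores could enter either one, and the protocol does not say whether change or follow-up scores are compared.

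**Conclusion.** The point holds in this limited form. The primary hypothesis and its effect measure are left to a pre-test on the outcome data, and one of the two branches does not, in general, test the 10.3-point mean difference behind the sample size. The chance of a split among 11 truly normal scores spans about 0% to about 68%, depending on a KS variant and a pooling choice that the article does not state. Rejection at zero mean difference rises to about 8-9% only under an assumed difference in shape and a Lilliefors gate. The required number of patients is unaffected. The matter is worth correcting because the remedy is cheap; it does not threaten the trial's validity.

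**What to change.** Delete the normality gate. For every quality-of-life score and the walk distance, pre-specify one analysis: the between-group mean difference at 12 months, adjusted for the baseline value of the same measure, with a 95% CI from HC3 robust errors. Report the rank-sum test as a labelled sensitivity analysis whatever the distribution looks like.

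Naming a single mean-difference analysis is what cures the defect. Baseline adjustment goes further, but it needs no new data because the Data collection section already has both questionnaires and the walk test recorded at screening.

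The cost is a wording change, a little more analysis work and no change in sample size. If scores prove strongly skewed, some power is lost relative to a rank test, as in step 6; baseline adjustment may recover part of it, but the protocol gives no correlation from which to say how much. The change should be made before outcome data are examined; the article reports that recruitment was still under way.

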## Methods/design

### Study design

The proposed clinical trial will be held at a single center, the Evandro Chagas Clinical Research Institute (IPEC), which is one of the technical scientific units of the Oswaldo Cruz Foundation (Fiocruz). IPEC is a 93-year-old institution fully dedicated to clinical research in infectious diseases, including Chagas disease, among others. IPEC is a major reference center for research, care, and training on Chagas disease.

This is a double-blinded, controlled, superiority (parallel) clinical trial with balanced randomization [1:1] that will be conducted for adult volunteers with Chagas disease complicated by HF. The patients’ functional status will be classified according the New York Heart Association (NYHA) functional classification system from I to IV. All patients at our institution are treated following current guidelines for diagnosis and management of HF in adults [12].

The cardiologists from our outpatient center will refer patients with chronic Chagas disease complicated by HF to the pharmacist. The pharmacist will explain the study in detail and obtain the patients’ informed consent. All included patients will undergo a screening phase, which includes a review of the patient’s medical records and an interview for assessment of eligibility. All eligible patients will complete quality-of-life questionnaires and take a six-minute-walk test after inclusion. After the screening phase, patients will be randomly assigned to one of two groups: an intervention group, who will receive standard care plus pharmaceutical care, and a control group, who will receive only standard care.

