### Data collection

At the screening phase, data regarding quality of life, six-minute-walk test results, DRPs, and clinical and sociodemographic data will be collected. Clinical and sociodemographicdata will include age, sex, functional class, heart rate, blood pressure, weight, Chagas serological test results, biochemical data (urea, creatinine, bilirubin, aspartate aminotransferase, alanine aminotransferase, and alkaline phosphatase levels), and comorbidities (hypertension, diabetes, and asthma), as well as alcoholism, smoking, and prescription drugs.

Data about DRPs will be collected at least once a month. At the end of the study follow-up, DRPs, six-minute-walk test results and MLHFQ and SF-36 scores will be collected again.

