### Randomization and concealment

A computer-generated random list of allocation, to either pharmaceutical care or standard care, will be generated, balancing 1:1. This assignment will occur within randomly ordered blocks of size four, six, or eight.

The allocation sequence will be concealed from the researchers enrolling and assessing participants, in sequentially numbered opaque, sealed, and stapled envelopes. To prevent subversion of the allocation sequence, the name and date of birth of the participant will be written on the envelope before the envelope is opened. The information in the envelope will be transferred to the allocation card inside the envelope. Corresponding envelopes will be opened only after enrolled participants have completed all baseline assessments and at the time of allocation. These procedures will be carried out by a professional without access to baseline evaluation results.

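### SF-36, MLHFQ and six-minute-walk distance are to be compared by a t or rank-sum test without adjustment for the baseline score that every patient provides, a valid choice that gives up precision

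*Protocol article*

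**What the plan says.** The method is stated outright under Statistical methods. The comparison is set out as follows: "The analysis strategy will be based on differences of MLHFQ and SF-36 scores", together with the drug-related problems outcome and walk distance, between control and intervention. For the questionnaires and the walk test, Student's t "test will be used if sample distribution proves to be normal". The alternative is equally plain: "Otherwise, the Wilcoxon rank-sum test will be used". No covariate, regression or ANCOVA appears.

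Baseline values exist for everyone. Study design says: "All eligible patients will complete quality-of-life questionnaires and take a six-minute-walk test after inclusion", and places this before random assignment. Data collection confirms it: "At the screening phase, data regarding quality of life, six-minute-walk test results, DRPs, and clinical and sociodemographic data will be collected". Randomization and concealment adds that envelopes are opened only once the baseline assessments are complete. At the end of follow-up, "six-minute-walk test results and MLHFQ and SF-36 scores will be collected again".

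On allocation, the list "will be generated, balancing 1:1", and "This assignment will occur within randomly ordered blocks of size four, six, or eight". No stratification factor is named.

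**The concern.** A patient's own baseline score is usually among the strongest predictors of the later score. Here it is collected on all patients, yet the named tests have no place for it as a covariate. Two things are at stake.

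- **Precision.** Variation between patients that the baseline could explain stays in the error term, so the confidence interval for the treatment difference is wider than it needs to be.
- **Chance imbalance.** With 44 patients per group and no stratification, the groups can differ at baseline by chance. A final-score test carries part of that difference into the estimate. A change-score test corrects too far.

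This does not rest on silence. The article names the test for the primary outcome, so the point concerns a choice that has been made.

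**Working it through.** **Inputs from the article (Sample size calculation and Table 1).** Difference 10.3 SF-36 points; SD up to 10.9; significance 1%; power 95%; 40 evaluable and 44 randomized per group.

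**Input not in the article.** The correlation r between baseline and 12-month score. It is assumed at 0.3, 0.5 and 0.7, with equal SDs at both times.

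**1. The plan's own figure.** n per group = 2 × SD² × (z for significance + z for power)² / difference².
- Two-sided 1%: 2 × 10.9² × (2.576 + 1.645)² / 10.3² = 39.9, so 40. This matches.
- One-sided 1%, as the text labels it: 2 × 10.9² × (2.326 + 1.645)² / 10.3² = 35.3, so 36. This does not match.

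The stated 40 therefore corresponds to a two-sided 1% test with the raw SD, that is, with no baseline adjustment. Two-sided 1% is used below. The mismatch in the label is a separate matter.

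**2. Variance relative to a final-score t test.** Final score: 1. Change score: 2(1 − r). ANCOVA: 1 − r².

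| r | Change | ANCOVA | ANCOVA vs final | ANCOVA vs change |
|---|---|---|---|---|
| 0.3 | 1.40 | 0.91 | 9% lower | 35% lower (0.91/1.40 = 0.65) |
| 0.5 | 1.00 | 0.75 | 25% lower | 25% lower (0.75/1.00 = 0.75) |
| 0.7 | 0.60 | 0.51 | 49% lower | 15% lower (0.51/0.60 = 0.85) |

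**3. Standard error of the difference, 40 per group.** Final score: 10.9 × √(2/40) = 2.44 points. Multiply by the square root of each factor above:

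| r | Final | Change | ANCOVA | 95% half-width (1.96 × SE), final to ANCOVA |
|---|---|---|---|---|
| 0.3 | 2.44 | 2.88 | 2.33 | 4.78 to 4.56 |
| 0.5 | 2.44 | 2.44 | 2.11 | 4.78 to 4.14 |
| 0.7 | 2.44 | 1.89 | 1.74 | 4.78 to 3.41 |

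**4. Power at the planned effect** (10.3/10.9 = 0.945 SD; 40 per group; noncentral t).

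| Level | Final score | ANCOVA, r = 0.3 | r = 0.5 | r = 0.7 |
|---|---|---|---|---|
| Two-sided 1% | 94.1% | 96.1% | 98.6% | 99.9% |
| Two-sided 5% | 98.7% | 99.2% | 99.8% | >99.9% |

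**5. Power at a smaller effect.** Half an SD, which is an assumption and not a figure in the article; two-sided 5%, 40 per group.

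| r | Final | Change | ANCOVA |
|---|---|---|---|
| 0.3 | 59.8% | 46% | 63.9% |
| 0.5 | 59.8% | 59.8% | 72.2% |
| 0.7 | 59.8% | 81% | 87.1% |

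**6. Chance imbalance, 44 per group.** The standard error of the baseline difference is √(2/44) = 0.213 SD. The chance of a difference above 0.25 SD in either direction is about 24% (0.25/0.213 = 1.17 standard errors). Taking a baseline SD of 10.9, an imbalance of 0.25 SD (0.25 × 10.9 = 2.7 points) shifts the final-score estimate by r × 2.7, that is 0.8, 1.4 and 1.9 points. It shifts the change-score estimate the other way by (1 − r) × 2.7, that is 1.9, 1.4 and 0.8 points. ANCOVA removes the expected shift in both cases.

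**The case against.** The strongest reply is that this is a matter of efficiency and not an error. A two-sample test between randomized arms controls type I error, and its estimate is unbiased over randomization. The sample size was set with raw SDs for exactly such a comparison, so design and analysis agree on this point. At the planned effect there is little power left to gain. All of this stands, and it limits the weight of the point.

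A reader might infer that the trial is underpowered. The article's own figures do not support that. The half-SD results in step 5 illustrate a smaller effect that the article does not posit; it expects at least ten points.

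A reader might also infer that nothing in the analysis deals with baseline imbalance. That goes too far, because the differences to be compared could be changes from baseline. The Outcomes section speaks of an increase in quality of life and the Discussion of an improvement, which suggest change. Table 1 compares group means using raw SDs, which suggests final scores. Against a change-score test the gain is smaller when r is high: at r = 0.7 and half an SD, 87% against 81%, not against 60%. Settling which score is tested is something an article may leave to a fuller document, so that gap is not counted here. The point holds on either reading, since ANCOVA has the smaller variance at each correlation examined.

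Unstratified blocked allocation at one center is an acceptable design and is not criticized.

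**Conclusion.** The point holds as a worthwhile gain in efficiency, not as a flaw in validity. The named tests leave out a baseline covariate that is available for every patient at no cost. The variance given up is 9% to 49% against a final-score test, or 35% to 15% against a change-score test, for r from 0.3 to 0.7. At the planned 10.3 points, power rises by only 2 to 6 percentage points at two-sided 1%, and by about 1 point at two-sided 5%. The practical benefit is a narrower interval, better power if the true effect is smaller than planned, and an estimate less exposed to chance imbalance. The Discussion describes this as the first such trial in Chagas heart failure, so a smaller effect than in the earlier heart failure work is worth guarding against.

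The sizes depend on r, which the article does not give, on equal SDs at both times, and on 40 patients analysed per group. The point-scale figures are for SF-36. The variance ratios apply equally to MLHFQ and walk distance at the same r.

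**What to change.** Amend Statistical methods, before anyone sees unblinded outcome data, so that the main analysis of SF-36, MLHFQ and six-minute-walk distance is ANCOVA: the 12-month value on group and the baseline value of the same measure, reporting the adjusted mean difference with its 95% confidence interval. The treatment coefficient is the same whether the 12-month value or the change is entered as outcome, so this also settles which of the two is tested.

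Drop the normality test as the switch between methods. Because the questionnaire scores are bounded and may be skewed, keep a rank-based analysis, for example rank ANCOVA, as a prespecified sensitivity analysis. NYHA class is not needed as a further covariate; the baseline score carries the argument.

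The cost is a short amendment to the protocol text, where the test is fixed, while the trial is still recruiting. It needs no new data, visits or patients, and the statistical package already named can fit the model.

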### Sample size calculation

Sample size calculation was based on previous work of the literature that evaluated pharmaceutical care and quality of life in patients with HF [21]. We estimated that 40 patients per group would be needed to detect a difference in quality of life on SF-36 of 10.3 points, allowing a standard deviation of up to 10.9 points, one-sided 1% significance, and 95% power. As we expect loss during follow-up of at least 10% of the study participants, 88 participants (44 per group) will be required (Table 1).

**Table 1 T1:** Sample size calculation according to scenarios of benefit in terms of quality of life for patients

**Parameter**	**Groups**		**Sample calculation**
	**Control group**	**Intervention group**	
Quality of life, mean (standard deviation)	52.8 (10.9)	63.1 (10.1)	
Significance level	1.0%	1.0%	
Power of test	95.0%	95.0%	
*N*	40 patients	40 patients	
*N* + 10% (in each group)	44 patients	44 patients	
Ratio	1:1	1:1	
Total	44	44	88

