## Abstract

**Background:**

Pharmaceutical care is the direct interaction between pharmacist and patient, in order to improve therapeutic compliance, promote adequate pharmacotherapeutic follow-up, and improve quality of life. Pharmaceutical care may be effective in reducing complications and in improving the quality of life of patients with chronic diseases, like Chagas heart disease, while bringing a positive impact on health system costs. The morbidity and mortality indexes for patients with Chagas heart disease are high, especially if this heart disease is complicated by heart failure. In this setting, we hypothesize that pharmaceutical care might be an important tool for the clinical management of these patients by improving their quality of life, as a better compliance to their treatment and the avoidance and prompt correction of drug-related problems will minimize their symptoms, improve their functional class, and decrease the number of hospital admissions. Therefore, the aim of this trial is to evaluate the contribution of pharmaceutical care to clinical treatment of patients with Chagas heart disease complicated by heart failure.

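### The loss allowance adds 10% to 40 instead of dividing 40 by 0.90, so 88 participants fall one short of the stated 80 at the stated minimum loss; the effect on power is small

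*Protocol article*

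**What the plan says.** The section on sample size calculation in the protocol article sets out three things.

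- The need: "We estimated that 40 patients per group would be needed to detect a difference in quality of life on SF-36 of 10.3 points". The planning SD is at most 10.9, and the error rates are set at "one-sided 1% significance, and 95% power".
- The expected loss and the resulting size: "As we expect loss during follow-up of at least 10% of the study participants, 88 participants (44 per group) will be required".
- The route from one to the other, in Table 1: N is 40 per group, and the next row adds 10% in each group to reach 44, for a total of 88.

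The loss is described as a share of the study participants, and 10% is given as a minimum.

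**The concern.** The three statements cannot all hold. If 40 per group are needed at the end and at least 10% of those enrolled are lost, 44 per group is too few. The usual cause is visible in Table 1: the allowance is taken as 10% of the patients needed, whereas the text defines it as 10% of the patients enrolled.

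What is at stake is the accuracy of the stated evaluable number. SF-36 and MLHFQ are repeated only at the end of the 12 months (Data collection), so a patient lost before then has no final score. Analysing patients as randomized does not by itself supply one.

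**Working it through.** **Inputs**, all from the sample size section and Table 1: 40 needed per group; difference 63.1 − 52.8 = 10.3; SD 10.9 (control) and 10.1 (intervention); 1% level, one-sided; 95% power; loss at least 10%; 44 per group, 88 in total.

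**Step 1. Reproduce the plan's figure.** 40 × (1 + 0.10) = 44 per group, and 2 × 44 = 88. This matches exactly.

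**Step 2. Apply the loss to those enrolled.** N/(1 − loss) = 40/0.90 = 44.4, rounded up to 45 per group, 90 in total. (Inflating the total gives 80/0.90 = 88.9, so 89, or 90 to keep 1:1.)

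**Step 3. See what 88 delivers.**
- Average at 10% loss: 88 × 0.90 = 79.2, or 44 × 0.90 = 39.6 per group.
- Whole patients: 8/88 = 9.1% is below 10% and 9/88 = 10.2% is above it. So at least 9 are lost and at most 79 remain, against the 80 needed.
- Largest loss that still leaves 40 per group: (44 − 40)/44 = 9.1%.

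**Step 4. Check where the 40 comes from.** Normal approximation: n = 2 × [SD × (z for the level + z for power)/difference]².
- One-sided 1%: 2 × [10.9 × (2.326 + 1.645)/10.3]² = 35.3, so 36 (37 by the t test).
- Two-sided 1%: 2 × [10.9 × (2.576 + 1.645)/10.3]² = 39.9, so 40.

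The 40 therefore matches a two-sided 1% level, not the one-sided level in the text. That is a separate inconsistency. It matters here only because power has to be shown on both readings.

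**Step 5. Power for a 10.3-point difference.** Two-sample t test, noncentral t with 2n − 2 degrees of freedom and noncentrality 10.3/(SD × √(2/n)). With SD 10.9 the noncentrality is 4.23 at n = 40, 4.17 at n = 39 and 4.06 at n = 37.

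| Evaluable per group | One-sided 1%, SD 10.9 | Two-sided 1%, SD 10.9 | Two-sided 1%, pooled SD 10.51 |
|---|---|---|---|
| 40 | 96.6% | 94.1% | 95.7% |
| 39 | 96.2% | 93.4% | 95.1% |
| 37 | 95.2% | 91.8% | 93.9% |
| 36 | 94.6% | 91.0% | 93.1% |

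The pooled SD is √[(10.9² + 10.1²)/2] = 10.51. With SD 10.9, going from 40 to 39 in both groups costs 0.4 points one-sided and 0.7 points two-sided. By the normal approximation at two-sided 1%, power is 95.05% at 40 and 94.8% at 39.6, a change of about 0.2 to 0.3 points. Reaching 37 per group takes a loss of 7/44 = 15.9%.

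**The case against.** The best defence is that the slip is too small to matter. At the stated minimum loss it is one patient in the whole trial: nine losses leave 79, for example 40 and 39. A difference of 44 against 45 is well inside the uncertainty of the planning SD. That stands, and it limits the weight of the point. It does not make the three statements consistent.

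Stronger conclusions are tempting, but the document does not support them.

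- *A reader might infer that the planned 95% power is lost.* On the stated one-sided 1% level with SD 10.9, power is 96.2% at 39 per group and above 95% down to 37. On the two-sided reading the t test already gives 94.1% at 40 with no shortfall, so most of that gap to 95% comes from the normal approximation behind the 40, not from the loss allowance. With the two SDs of Table 1 pooled, 39 per group still gives 95.1%.
- *A reader might infer that both groups drop to 39 at 10% loss.* That takes ten losses, 10/88 = 11.4%.
- *A reader might infer that loss will run well above 10%,* because the abstract says: "The morbidity and mortality indexes for patients with Chagas heart disease are high". That sentence gives no loss rate. The eligibility criteria exclude NYHA class IV and survival-limiting comorbidities, and missed visits are followed up by telephone. Any figure above 10% is an assumption.

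**Conclusion.** A minor arithmetic error, certain as arithmetic. The stated 88 does not deliver the stated 40 per group at the stated minimum loss: it covers 9.1%, and 10% would need 45 per group. The shortfall at the minimum is one patient overall, and the trial's ability to detect 10.3 points is essentially unchanged.

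This rests on two readings: that the 10% refers to participants enrolled, as the text says, and that a lost patient contributes no 12-month questionnaire score. The power figures further assume a true difference of 10.3 points and the SDs of Table 1.

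**What to change.** Correct the sample size section and the Table 1 row that adds 10%, without enrolling more patients:

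- State that 88 participants leave about 79 evaluable (39.6 per group on average) at 10% loss.
- State that 44 per group covers a loss of up to 9.1%, and that 40 evaluable per group at 10% loss would need 45 per group (90 in total).
- Give the power at the evaluable number that remains, naming the significance level, sidedness and SD used.

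Because 10% is given as a minimum, the sponsor may also show power at one or two higher loss rates, labelled as assumed. This is optional.

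The cost is a few words and one table row. Enrolment and analysis do not change, and the stated evaluable number becomes slightly less favourable.
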